# A guaranteed income intervention to improve the health and financial well-being of low-income black emerging adults: study protocol for the Black Economic Equity Movement randomized controlled crossover trial

**DOI:** 10.3389/fpubh.2023.1271194

**Published:** 2023-11-03

**Keywords:** guaranteed income, Black young adult, economic empowerment, cross-over trial, cash transfer, socioeconomic disparities in health, systemic racism

## Abstract

**Background:**

Economic inequity systematically affects Black emerging adults (BEA), aged 18–24, and their healthy trajectory into adulthood. Guaranteed income (GI)–temporary, unconditional cash payments–is gaining traction as a policy solution to address the inequitable distribution of resources sewn by decades of structural racism and disinvestment. GI provides recipients with security, time, and support to enable their transition into adulthood and shows promise for improving mental and physical health outcomes. To date, few GI pilots have targeted emerging adults. The BEEM trial seeks to determine whether providing GI to BEA improves financial wellbeing, mental and physical health as a means to address health disparities.

**Methods/design:**

Using a randomized controlled crossover trial design, 300 low-income BEA from San Francisco and Oakland, California, are randomized to receive a $500/month GI either during the first 12-months of follow-up (Phase I) or during the second 12-months of a total of 24-months follow-up (Phase II). All participants are offered enrollment in optional peer discussion groups and financial mentoring to bolster financial capability. Primary intention-to-treat analyzes will evaluate the impact of GI at 12 months among Phase I GI recipients compared to waitlist arm participants using Generalized Estimating Equations (GEE). Primary outcomes include: (a) financial well-being (investing in education/training); (b) mental health status (depressive symptoms); and (c) unmet need for mental health and sexual and reproductive health services. Secondary analyzes will examine effects of optional financial capability components using GEE with causal inference methods to adjust for differences across sub-strata. We will also explore the degree to which GI impacts dissipate after payments end. Study outcomes will be collected via surveys every 3 months throughout the study. A nested longitudinal qualitative cohort of 36 participants will further clarify how GI impacts these outcomes. We also discuss how anti-racism praxis guided the intervention design, evaluation design, and implementation.

**Discussion:**

Findings will provide the first experimental evidence of whether targeted GI paired with complementary financial programming improves the financial well-being, mental health, and unmet health service needs of urban BEA. Results will contribute timely evidence for utilizing GI as a policy tool to reduce health disparities.

**Clinical trial registration:**

https://clinicaltrials.gov, identifier NCT05609188.

## Introduction

The significant physical, emotional, and developmental changes that occur during the developmental period of emerging adulthood (ages 18–24) put young people at risk for increased mood disorders, increased risk-taking behaviors, and decreased health-seeking behaviors (1–6). Poverty, driven by deep systemic social and structural inequities, exacerbates these negative outcomes and upends the safe and healthy transition to adulthood (7, 8). The impacts of poverty are acute for Black adolescents and young adults, under the age of 25 years. Compared to White adolescents and young adults, Black adolescents and young adults in the U.S. experience higher levels of poverty, illness, and discrimination (9–11). These exposures to harm, coupled with the lack of supportive services to address and mitigate poverty and structural inequities, result in disproportionately adverse mental and physical health outcomes. Black adolescents and young adults report high mental health service needs (12, 13), but receive services at a lower rate than other racial groups of the same age (14–16)–over half (58%) of Black adolescents and young adults with a serious mental illness report not receiving treatment in the past year (17). In terms of physical health, Black adolescents and young adults account for nearly 60% of new HIV infections within their age group in the U.S. (18), despite comprising 14% of the total adolescent and young adult population. Black adolescents and young adults experience gonorrhea at eight times the rate of their White peers and chlamydia at four times the rate of White peers (19, 20). Disrupting the social determinant of poverty that systematically affects young people during the critical developmental period of emerging adulthood can have a transformative impact on their mental and physical health, and their trajectory into adulthood.

Envisioning a more equitable and healthy future for Black emerging adults (BEA) (ages 18–24) requires bold, multilevel interventions that address structural-level factors, including poverty and racism, and their fundamental impacts on health (21, 22). Structural racism and the resulting socioeconomic inequality has limited the opportunities for Black Americans for generations, through a number of institutional and policy-level mechanisms (i.e., Jim Crow laws and ongoing discrimination in housing, hiring and lending) that reduce access to wealth and health (23–25). Over the past 30 years, the average wealth of White families has grown at three times the rate of growth for Black families (26). Further, economic programs in the U.S. historically have tied income assistance to work (e.g., welfare to work, unemployment), which restricts who can access assistance and how it is used and require lengthy applications (27), all of which obstructs a path out of poverty.

Upending poverty and economic inequity requires providing BEA the security, time, and supports needed to enable their transition into financial independence, including support to invest in long-term financial well-being, such as educational and occupational training. One approach to transforming structural inequities is providing a guaranteed income (GI), without contingencies or burdensome requirements. GI, rooted in racial justice movements (28, 29), has been proposed as a strategy to counteract the effects of structural racism and years of disinvestment in Black communities (30). Pilot GI programs tested with low-income adults have shown impressive gains in economic security that have impacted markers of health and well-being. For example, the Stockton Economic Empowerment Demonstration (SEED) project, a GI program based in Stockton, California, that gave selected residents $500 per month, increased recipients’ full-time employment and decreased anxiety and depression, after 1 year (31). Past GI experiments have found that adolescents in households that received GI were more likely to continue schooling than non-recipient households (32–34). A recent systematic review of guaranteed income studies in high-income countries also found consistent and clear improvements in mental health coupled with reductions in stress and hope for the future (35). Early evidence from these programs have resulted in support for GI projects in cities across the United States (36).

Within the nascent GI movement in the US, GI programs are quickly expanding among some subpopulations of young adults (e.g., young adults experiencing homelessness) (37, 38), although they have rarely been rigorously evaluated during the critical transitional period of emerging adulthood. Programs that did target adolescents and young adults have largely been conditional (requiring engagement in a specific behavior) (39, 40), directed payments to the family rather than adolescents and young adults themselves (40, 41), or were of limited scientific scope and size (42, 43). Providing GI to BEA could transform their opportunities as they develop their educational, employment, and financial trajectories and before financial challenges lead to deepening debts or abandoning educational pathways. Further, impacts of GI programs could be maximized with multilevel supports, such as financial mentoring, peer support, and immediate service referral, to elevate emerging adults’ capacity to attain the financial stability required to support their mental and physical health (44–46).

To address these gaps in scientific knowledge, we designed a randomized controlled crossover trial to assess the efficacy of a multilevel GI intervention among low-income BEA to improve the immediate and future mental and physical health outcomes of BEA and to support BEAs’ agency and independence. Recognizing of the developmental needs of emerging adults, the intervention will provide access to financial capability programs through mentoring (individual level) and peer discussion groups (interpersonal level) in addition to providing BEA with GI. Furthermore, we lack critical knowledge of if and how the impacts of GI are sustained (47). To address this gap, this study will also evaluate outcomes one-year after GI payments end and explore potential mediators, contributing to knowledge of the impact of GI on BEAs’ trajectories over time. Finally, being that this is one of the first GI studies with emerging adults, we will closely track social harms to ensure that we can report on any potential downsides of providing GI to emerging adults. Notably, there is more speculation around potential negative effects, such as de-incentivizing work, than empirical data to support these concerns.

Although efforts to address the health impacts of structural racism through public health interventions have grown (48), the literature on incorporating anti-racism praxis into research methodology has been limited (49), focusing on certain areas such as conceptualizing race or community engagement. Anti-racism praxis is the reflexive process of dismantling racism in actions and systems (50). Failure to critically consider race and equity in study design and implementation can inadvertently perpetuate structural racism through research. We prioritized racial equity in our approach; we share examples of how we sought to weave anti-racist approaches into the design of the GI intervention, the design of the evaluation, and implementation of the project.

## Methods

### Trial design

The BEEM trial design is mixed methods, comprised of the quantitative randomized controlled crossover trial with a complementary, nested qualitative component including longitudinal semi-structured in-depth-interviews with a subset of participants to explain the processes that drive the results of the intervention (see Figure 1) (51). We aim to determine the impact of GI on three related sets of primary and secondary outcomes: (a) financial well-being (investing in education and training, savings, debt, financial capability); (b) mental health (depressive symptoms, anxiety, hope/future orientation); and (c) utilization of mental health and sexual and reproductive health (SRH) services. For the trial, 300 low-income BEA are randomized 1:1 to receive 12 months of GI either (a) during the first 12 months of follow-up (Phase I) or (b) in the second 12 months of a total of 24 months follow-up (Phase II). Most GI evaluations have used either parallel-group RCT designs, withholding GI from control groups, or rely on quasi-experimental (pre-post) designs. To address equity in the study, we employ a crossover randomized controlled design to ensure all participants in the project receive GI and offer peer discussion and financial mentoring to all participants. This allows us to implement a rigorous study design to draw causal inferences while centering BEA needs. The addition of opt-in financial capability programs allows us to explore whether complimentary supports can enhance GI while simultaneously respecting BEAs’ autonomy to choose when and how to engage with supports. An additional benefit of the crossover design is that it allows us to not only determine the impact of GI alone, but also sustained impacts once GI is concluded, thus addressing an important knowledge gap regarding sustainability in the evidence for GI programs. This protocol is written according to the Standard Protocol Items Recommendations for Interventional Trials (SPIRIT) 2013 statement (52), an international standard for trial protocols.

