### Research hypotheses

Our primary research question is to understand the potential impacts of GI on BEAs investment in their future (education, employment, training), mental health (depressive symptoms), and unmet mental health (MH) and sexual/reproductive health (SRH) service needs. We are also interested in learning if complementary financial supports propel greater impact on health outcomes and understanding to what degree GI impacts dissipate after the transfers end. Thus, our hypotheses are as follows.

*H1*: *GI will improve all outcomes*. Youth receiving GI in phase I will have greater increases in investments in their future (H_1a_), greater decreases in depressive symptoms (H_1b_), and larger reductions in unmet need for MH and SRH services (H_1c_) at 12 months than those who do not received GI in phase I.

*H2*: *GI + financial supports will improve outcomes more than GI alone*. Participants receiving GI in phase I who participate in mentoring or peer discussion groups will have greater increases in investments in their future (H_1a_), greater decreases in depressive symptoms (H_1b_), and larger reductions in unmet need for MH and SRH services (H_1c_) at 12 months than those not opting into financial support programs.

*H3*: *Gains from GI will be sustained*. Participants receiving GI in phase I will not experience a decline in odds of enrollment in educational/training programs (H_3a_) or an increase in odds of depressive symptoms (H_3b_) or unmet need for MH and SRH services (H_3c_) following the removal of GI (between month 12 and 24).

*H4*: *Accessing complementary financial supports prior to receiving GI will improve overall outcomes.* Among BEA who do not receive GI in phase I, those who engage in mentoring or peer discussion groups in phase I will have greater increases in investments in their future (H_4a_), greater decreases in depressive symptoms (H_4b_), and larger reductions in unmet need for MH and SRH services (H_4c_) at 24 months than BEA who did not opt-in into the financial programming prior to receiving GI.

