#### Secondary analyses

We will determine if BEA receiving GI in Phase 1 who opt-in to peer discussion groups and financial mentoring will have larger increases in odds of investment in the future, larger declines in odds of depressive symptoms and larger declines in odds of unmet mental and sexual health service needs at 12 months compared to those who did not opt into these support programs (H2). We will use the same modeling approach as described above for H1 used to test H2 except that analysis will be restricted to a single arm of the study (those receiving GI in phase I or those receiving GI in phase II).

As in our preliminary analyses, we will employ causal inference methods to adjust for any differences between sub-strata [e.g., individuals who do or do not opt in to financial mentoring or peer discussion groups at baseline or due to differential loss to follow-up]. As in our primary analyses, we will use logistic GEE to model our dichotomous outcomes, and continuous GEE specifications for continuous measures. We will test H2 via DID comparison of post-baseline measurements in the Phase 1 GI group during Phase 1 (as in H1). All comparisons for secondary analyses (H2 through H4) will be tested at *α* = 0.05 per comparison.

We will test (H3)–BEA receiving GI in Phase 1 will not experience a significant decline in odds of enrollment in educational or training programs, a significant increase in odds of depression or a significant increase in odds of unmet mental and sexual health service needs following removal of the GI (between month 12 and 24)–using an interrupted time series (ITS) approach. For these ITS analyses, we will include indicators for phase, time and the interaction between phase and time to examine the slope in each outcome during Phase 1, the presence of an immediate change in each outcome after removal of GI (level effect), as well the change in slope for each outcome during Phase 2 (slope). If changes in outcomes do not follow a linear trend, we will explore alternative relationships including polynomial and spline terms.

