## Discussion

The BEEM Project addresses the important impact of decades of structural racism and inequitable access to opportunity and wealth generation for BEA, while also addressing scientific knowledge gaps regarding the impacts of GI on financial well-being and health outcomes. The randomized controlled crossover design supports the ability to draw causal inferences while ensuring all participants have access to no-strings-attached cash payments. This study will illuminate the impacts of complementary financial capability programming (i.e., mentoring, peer discussion groups) and their ability to bolster the effects of GI as an accompanying policy program. The extended data collection period will aid understanding of sustained impacts of GI one-year after payments end, filling a critical gap in knowledge on the degree to which the impacts of GI dissipate (follow-up for most GI projects have rarely extended beyond a few months). Results about the extended impact of GI can also provide evidence about augmenting health trajectories over the life course.

Importantly, results of the study will also help determine the utility of GI as a strategy to tackle racial health disparities. The focus of our project is on empowering low-income BEA, a group that has been made vulnerable by a history of intersecting social, economic, and political systems that result in lasting economic inequities and denied opportunities. This study will provide evidence about targeting GI within a group whose financial vulnerability and health inequalities have been created by structural racism and impact health transitions to adulthood. We apply anti-racism praxis and actively engage with communities, an approach vital for informing our approaches to affirming the autonomy of BEA, allocating and distributing resources, and challenging institutional (including research) norms.

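### The crossover is credited with showing sustained GI impact, but H3 is a single-arm time series with no GI-free comparator after month 12 and a treated year as its pre-period

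*Protocol article*

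**What the plan says.** The Trial design section of the protocol article states that "300 low-income BEA are randomized 1:1 to receive 12 months of GI either (a) during the first 12 months of follow-up (Phase I") or "in the second 12 months of a total of 24 months follow-up (Phase II"). It then says without qualification that an "additional benefit of the crossover design is that it allows us to not only determine the impact of GI alone, but also sustained impacts" after GI ends. The Introduction promises that "this study will also evaluate outcomes one-year after GI payments end", and the Discussion says that the extended follow-up will aid understanding of "sustained impacts of GI one-year after payments end".

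The test of this is H3. Under Research hypotheses it reads "Participants receiving GI in phase I will not experience a decline in odds of enrollment in educational/training programs", with matching statements for depression and unmet need, between months 12 and 24. Under Secondary analyses the method is an interrupted time series (ITS): "we will include indicators for phase, time and the interaction between phase and time". The quantities of interest are the Phase 1 slope, a level change when GI stops, and a change in slope in Phase 2. Polynomial or spline terms may be used if trends are not linear. The hypothesis is worded as no significant decline (or no significant increase for the adverse outcomes), each comparison is tested at 0.05, and no margin is given.

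The limitations paragraph of the Discussion says that this ITS is open to other time shocks, which will be monitored.

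**The concern.** An impact is a difference from what would have happened without GI. In year 1 the waitlist arm supplies that reference. In year 2 it does not, because it is then receiving GI. H3 does not work around this. Its population is the Phase 1 GI arm and its model has no arm term, so the same analysis could be run in a trial with no second arm. It is in substance a pre-post comparison, the kind of design that the Trial design section contrasts with this trial.

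An ITS also needs a pre-interruption segment that shows the course to be projected forward. Here that segment is the year in which GI starts and takes effect. Its slope therefore contains both the growth of the GI effect and any background change in young adults who age two years during the study.

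At stake is the conclusion on sustainability, which the article presents as a knowledge gap that the trial fills. The primary hypothesis, H1, is a randomised year-1 comparison and is not affected.

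**Working it through.** The article gives no power, margin or expected trend for H3, so there is no stated figure to reproduce.

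**Inputs**
- From Sample size estimation: 10.7 points (upper end of the detectable difference for enrollment and depression), ICC 0.20 to 0.80, 25% attrition over 12 months.
- From Trial design: 300 participants, 150 per arm.
- Assumed: the shapes of the GI effect, background shifts of ±10.7 points, a 40% starting rate, and retention held at 75% to month 24.

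**Step 1. H3 terms without noise.** I fitted intercept, time in quarters, phase, and phase × time to quarterly points at months 0 to 24 on the risk scale, for an outcome where higher is better. The level change is read at month 15, the first post-GI survey.

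| Phase 1 arm | Background | Level change | Slope change per quarter |
|---|---|---|---|
| Builds linearly to 10.7 by month 12, fully kept | flat | -2.7 | -2.7 |
| Immediate 10.7, fully kept, baseline in Phase 1 slope | flat | -4.3 | -2.1 |
| Immediate 10.7, fully kept, baseline left out | flat | 0.0 | 0.0 |
| Immediate 10.7, fully lost after month 12, baseline left out | flat | -10.7 | 0.0 |
| Same loss, baseline left out | linear, ±10.7 a year over both years | -10.7 | 0.0 |
| Same loss, baseline left out | +10.7 shift in year 2 | 0.0 | 0.0 |

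Row 1 by hand: the Phase 1 slope is 10.7 / 4 = 2.7 per quarter and the Phase 2 slope is 0, so the change is -2.7. Projected to month 24, the Phase 1 trend expects 21.4 points, against 10.7 observed. If the level is read at month 12, the level change is 0.0 and the slope change is still -2.7.

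Rows 3 and 6 are the same observed curve: full persistence on a flat background, and full loss with a favourable shift of equal size. No term or spline can separate identical curves.

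Row 5 shows the limit of the problem. A trend that is linear over both years is absorbed by the Phase 1 slope, and an abrupt loss still shows.

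**Step 2. Simulated H3 model.** Logistic GEE, 150 people, exchangeable correlation, about 82 runs per case (error about 5 points).
- Fully kept, flat background (rows 1 and 2): at least one significant negative term in 27% of runs at ICC 0.2 and 51-77% at ICC 0.8.
- Abrupt full loss, flat background: no significant negative term in 17-49% at ICC 0.2 and 0-9% at ICC 0.8.
- Abrupt full loss with a +10.7 year-2 shift, baseline included: no significant negative term in 70-72% and 24-32% respectively.

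**Step 3. What both arms can give.** Let D be the Phase 1 arm minus the Phase 2 arm, τ the effect of 12 months of GI, and λ the effect remaining a year after it ends. If τ is the same in either year:
- D12 = τ
- D24 = λ - τ
- D12 + D24 = λ

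A background common to both arms cancels. In a related simulation (between-arm change from baseline to months 15-24, 300 runs per case), the contrast averaged -0.1 to 0.9 points when the impact was kept and -10.2 to -11.5 when it was lost, under every background tried. A significant negative contrast appeared in 1-4% of runs when kept. When lost, it appeared in 35-42% at ICC 0.2 and 69-88% at ICC 0.8.

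**Step 4. Precision of D12 + D24.** With about 112 per arm (150 × 0.75 = 112.5) and correlation r = 0.47 between months 12 and 24, each arm contributes [p12·q12 + p24·q24 + 2r·√(p12·q12·p24·q24)] / 112, where q = 1 - p.
- Depression, assumed 26%/26% against 34%/18%: (0.566 + 0.543) / 112 = 0.0099, SE 0.099, 95% CI ±19 points.
- Enrollment, assumed 50%/40% against 40%/40%: (0.720 + 0.706) / 112 = 0.0127, SE 0.113, 95% CI ±22 points.

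**The case against.** The strongest reply is that H3 is an ITS and not a raw comparison of month 24 with month 12. It projects the arm's own Phase 1 trend, so steady maturation is largely removed. This stands. A reader might infer that any natural trend in this age group decides the H3 result whichever ITS term is tested. The documents do not support that. A false reading of persistence needs a departure from trend in year 2, low power, or reliance on the raw change that H3's month 12 to 24 wording invites. The false reading of decline needs less: a plateau after build-up is enough.

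Second, the limitations paragraph discloses time shocks, and splines are allowed. The disclosure covers an external shift around month 12. It does not mention the missing comparator, maturation or the treated pre-period, and it leaves the Trial design claim unqualified. Splines do not restore a comparator.

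Third, D12 + D24 is no clean substitute. In year 2 the waitlist arm is a year older, has anticipated the payments, and may have had a year of mentoring or peer groups. Equal effect in both years cannot be tested here, and an interval of about ±20 points cannot resolve an effect of 8 to 10 points. This stands too, so the estimate can only support the claim and should not be its sole permitted basis.

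Finally, no sentence excludes the waitlist arm from H3; that is inferred from the stated population and model terms. A fuller plan may hold a between-arm analysis. The point rests on what the article itself fixes: the design claim, the hypothesis, its population and its terms.

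**Conclusion.** The concern holds in a limited form. The article attributes the sustained-impact conclusion to the crossover, but the specified H3 analysis draws nothing from it, and after month 12 no arm is free of GI exposure. A fully kept 10.7-point impact that built up linearly over year 1 shows a slope change of about -2.7 points per quarter on a flat background. A full loss masked by an equal favourable year-2 shift cannot be distinguished from full persistence. A background that is linear across both years does not cause the problem.

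The sizes rest on an illustrative 10.7-point effect, assumed effect shapes and assumed background shifts, since the article gives no background trend. H3 is secondary and H1 is untouched. This should be corrected, but it does not threaten the primary result.

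**What to change.** 1. In the Introduction, Trial design, Research hypotheses (H3) and Discussion, describe H3 as change in the Phase 1 GI arm after payments end. Qualify the statement that the crossover determines sustained impact.
2. Extend the limitations paragraph to name the missing no-GI comparator in year 2, maturation, and the use of a treated year as the pre-interruption segment.
3. Add a supporting between-arm analysis using both arms over months 0 to 24. Report the randomised month-24 difference (GI first versus GI later) and the residual effect D12 + D24, on the risk-difference scale with confidence intervals. State the assumption that GI has the same effect in either year.
4. State that sustained impact will not be concluded from a non-significant single-arm change alone.

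The cost is wording and one further model. Both arms are already surveyed quarterly for 24 months, so no new data are needed. The downside is a weaker sustainability conclusion, because the between-arm estimate is imprecise and depends on the equal-effect assumption.
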